# 9.2.4. Safety analysis:

Safety analysis is taken based on SS data set.

Data of adverse events (case number, times and incidence of various adverse events) are compared between the two groups. At the same time, detailed description of specific manifestation, extent of all adverse events and the relation with drugs would be further analyzed.

Crosstab is adopted to describe the change of laboratory index. Number of normal cases before treatment, number of abnormal cases after treatment and ratio of abnormal cases are analyzed in study group and control group. Indexes of vital signs are compared between before and after treatment.

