| **Outcome Measures** | Primary endpoints | The composite endpoint events consisting of cardiovascular death and re-hospitalization due to the worsening of heart failure |
| Secondary endpoints | 1. All-cause mortality 2. Secondary endpoint events (given up treatment due to worsening heart failure, successful resuscitation after cardiac arrest, malignant arrhythmia, non-fatal stroke) 3. The incidence of cardiovascular death and re-hospitalization due to worsening heart failure in patients with ischemic heart disease 4. Serum NT-proBNP decrease rate |
| Safety objective and measure | To evaluate the safety and tolerability of QLQX in this patient population;  Changes in clinical chemistry/haematology parameters, ECG, physical examination, any forms of adverse events (AEs) |
| **Statistical methods** | The primary objective of the study is to determine the superiority of QLQX versus placebo in reducing the incidence of the primary composite endpoint. The random distribution ratio is 1:1 between study group and control group. The sample size is in estimating the incidence of composite endpoint events for 25% during the follow-up period of 36 months. In total 3080 cases were expected to enroll (1540 patients per group) with 620 composite endpoint events should be observed. | |
| **Statistical unit** | Peking University Clinical Research Institute | |
| **Dosage and mode of administration** | Study group: Standardized treatment of chronic heart failure + Qiliqiangxin Capsules, 4 capsules/time, 3 times/day, take orally  Control group: Standardized treatment of chronic heart failure + Placebo Capsules, 4 capsules/time, 3 times/day, take orally | |
| **Duration of treatment** | The patient was enrolled with observation event as the index. The planned enrollment time was 2 years and the drug was taken for at least a year. | |
| **Expected progress** | August 2018 to August 2021 | |

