# 2.3.2 . Exclusion criteria

1. Patients should not enter the study if any of the following exclusion criteria are fulfilled
2. Heart failure caused by valvular disease, congenital heart disease, pericardial disease, arrhythmia or non-cardiaogenic disease, or caused by vital organ failure (such as renal, hepatic failure, etc.); and right heart failure caused by pulmonary or other definite causes; and acute heart failure;
3. Coronary revascularization (percutaneous coronary intervention [PCI] or coronary artery bypass grafting [CABG]) or cardiac synchronization therapy planned to undergo after randomization, or had received cardiac resynchronization therapy prior to enrolment;
4. Any condition outside the CV diseases such as but not limited to malignant tumor, severe mental illness, hematopoietic diseases, neuroendocrine system disease, liver transaminase and alkaline phosphatase ≥ 3 x upper limit of normal (ULN), abnormal renal function serum creatinine > 2 mg/dl (176.82 umol/L), potassium >5.5mmol/L;
5. Patient with left ventricular outflow tract obstruction, myocarditis, aortic aneurysm, aortic dissection, or obvious hemodynamic changes caused by unrepaired valve;
6. Cardiogenic shock, uncontrollable malignant arrhythmia, sinus or atrioventricular block at second degree type II or above without pacemaker treatment, progressive unstable angina pectoris or acute myocardial infarction;
7. uncontrolled hypertension systolic blood pressure (SBP) ≥ 180mmHg and/or diastolic blood pressure (DBP) ≥ 110mmHg; or SBP < 90mmHg and/or DBP <60mmHg;
8. Participation in another clinical study with an IP during the last month prior to enrolment;
9. Women of child-bearing potential (i.e., those who are not chemically or surgically sterilized or who are not post-menopausal) who are not willing to use a medically accepted method of contraception that is considered reliable in the judgment of the investigator, from the time of signing the informed consent throughout the study and 4 weeks thereafter, OR women who have a positive pregnancy test at enrolment or randomisation OR women who are breast-feeding;
10. Allergic constitution; known to be allergic to research drug;
11. Inability of the patient, in the opinion of the investigator, to understand and/or comply with study medications, procedures or any conditions may render the patient unable to complete the study.

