# 4.2. Safety outcome measure:

- Adverse events (Serious Adverse Events [SAEs], Discontinuation of IP due to Adverse Events, etc.)
- AEs of interest (volume depletion, renal events, etc.)
- Clinical laboratory indexes: blood routine test (hemoglobin, red blood cells, white blood cells, platelets), routine urine test (urinary protein, urinary white blood cells, urine red blood cells), serum biochemistry (urea nitrogen, creatinine, blood uric acid, total protein, albumin, alanine aminotransferase, aspartate aminotransferase, alkaline phosphatase, total bilirubin, fasting blood glucose, potassium, sodium, chlorine, total cholesterol, triglycerides, low density lipoprotein, high density lipoprotein).
- 12-lead ECG
- Physical examination

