# 7.4. Adverse events based on examinations and tests

The results from protocol mandated laboratory tests and vital signs will be summarized and give possible interpretation. The abnormal laboratory results caused by reported adverse events should be recorded in the adverse event form. The abnormal results with clinical significance that meets one or more following conditions should be recorded as independent diagnosis on adverse event page of CRF (excluding abnormal laboratory result caused by reported adverse events):

- With associated clinical signs and symptoms
- Change in course of study drug’s treatment dose
- Change in any of standard evidence based medications and (or) other treatment measures need to be changed

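### The laboratory crosstab in Protocol Section 9.2.4 cannot show further worsening in patients already abnormal at entry, or shifts within the normal range

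*Protocol*

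**What the plan says.** - **Analysis.** Protocol Section 9.2.4 states the laboratory method: "Crosstab is adopted to describe the change of laboratory index". It then names what is tabulated in the two groups: "Number of normal cases before treatment, number of abnormal cases after treatment and ratio of abnormal cases are analyzed". It mentions no grade, no abnormal-to-worse category and no change in the measured value.
- **Measure.** The synopsis gives the safety measure as "Changes in clinical chemistry/haematology parameters, ECG, physical examination, any forms of adverse events (AEs".
- **Data.** Section 4.2 collects "serum biochemistry (urea nitrogen, creatinine, blood uric acid" and, in the same list, potassium and sodium. A separate bullet lists "AEs of interest (volume depletion, renal events, etc".
- **Entry limits.** Section 2.3.2 excludes "abnormal renal function serum creatinine > 2 mg/dl (176.82 umol/L), potassium >5.5mmol/L". It sets no limit on urea or sodium and no lower limit on potassium.
- **Adverse events.** Section 9.2.4 also says: "Data of adverse events (case number, times and incidence of various adverse events) are compared between the two groups". Section 7.4 adds: "The abnormal results with clinical significance that meets one or more following conditions should be recorded as independent diagnosis on adverse event page of CRF". The conditions are associated signs or symptoms, a change in study-drug dose, or a change in standard medication or other treatment. Section 7.4 also provides for a summary of the mandated laboratory results.

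**The concern.** The measure is change in laboratory parameters, but the one tabulation spelled out reduces each value to normal or abnormal. A patient who enters with creatinine, urea or potassium already outside the normal range cannot move from normal to abnormal, however far the value then moves. A sizeable rise that ends inside the normal range is also invisible.

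This matters because the protocol itself singles out volume depletion and renal events. Section 1.3 also attributes a diuretic effect to the drug, although that text goes on to work in rats. If the drug caused a modest silent drift in creatinine or potassium in patients with impaired values at entry, the laboratory table could look balanced while the underlying values diverged between the arms.

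**Working it through.** The protocol gives no figure to reproduce. The check sets its sections side by side, with arithmetic for illustration only.

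**1. What the table can register.** Two classes before and two after treatment give four cells:

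| Before | After | Registered as |
| --- | --- | --- |
| normal | normal | no change, whatever the size of the shift |
| normal | abnormal | new abnormality (the count that Section 9.2.4 points to) |
| abnormal | normal | improvement |
| abnormal | abnormal | no change, however far the value worsens |

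Printing the abnormal-before row helps with completeness, but the last cell still cannot separate stable from worse.

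**2. Whether patients can start abnormal.** Section 2.3.2 excludes only creatinine above 176.82 umol/L and potassium above 5.5 mmol/L. Patients with raised creatinine up to that cap, or with any abnormal urea, sodium or low potassium, are not excluded by a laboratory limit. The protocol does not say how many there will be.

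**3. Illustration for creatinine.** The protocol gives no upper limit of normal; take 106 umol/L as an assumption.
- From 80 to 106: 106/80 = 1.325, a rise of 32.5%, still normal and not registered.
- From 96 to just above 106: 106/96 = 1.104, a rise of about 10.4%, registered as a new abnormality.
- From the entry cap of 176.82 to twice that value: 2 × 176.82 = 353.64, a rise of 100%, abnormal to abnormal and not registered in the table.

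The table therefore follows distance from a fixed limit, not size of change.

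**4. Illustration of how many patients.** If 10% to 40% of the planned 3080 started abnormal on a given test (an assumption), then 0.10 × 3080 = 308 and 0.40 × 3080 = 1232 patients could not contribute a normal-to-abnormal shift on that test.

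**5. What other routes exist.**
- Renal events reported as adverse events are compared by number and incidence, with no condition on the baseline value.
- A clinically significant abnormal result that meets a Section 7.4 condition goes to the adverse event page and so into that comparison, again whatever the baseline.
- Section 7.4 says laboratory results are summarised, and Section 9.2 lists the descriptive statistics for quantitative data. Neither names a between-arm comparison of laboratory change. By contrast, Section 9.2.3 gives NT-proBNP a between-group analysis of the measured values, and Section 9.2.4 compares vital signs before and after treatment.

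**6. What remains.** Worsening without symptoms or treatment change in patients abnormal at entry, and shifts within the normal range in anyone, reach no between-arm analysis that the protocol names.

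**The case against.** The strongest reply is that Section 9.2.4 has to be read with Sections 4.2 and 7.4. A reader might infer that renal events of interest are analysed only through the normal-to-abnormal table. They are not: Section 4.2 lists them as adverse events, apart from the laboratory indexes, and adverse events are compared between the groups. A reader might also infer that worsening in patients abnormal at entry is never counted. That too fails, because clinically significant worsening with symptoms or a treatment change is recorded and compared as an adverse event.

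The wording in Section 9.2.4 is a translation and does not expressly confine the abnormal-after count to patients who were normal before. A full crosstab would include the other row. A statistical analysis plan is foreseen but not shown, and graded shifts and change-from-baseline tables are often placed there.

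A reader might also want to quote a power figure for the crosstab against an analysis of continuous change. That would need a baseline distribution, a normal limit and a within-patient variability, none of which the protocol gives. It would also treat a table meant as description as a hypothesis test. If the effect is placed only in patients abnormal at entry, the normal-to-abnormal count fails by construction. Such figures are not properties of this trial.

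All of this stands and narrows the point, but does not remove it. The adverse event route depends on judged clinical significance plus a listed condition. Section 7.1.3, despite its heading on events of interest, contains only causality grading and gives no laboratory criterion for a renal event. On any reading of the crosstab, abnormal-to-abnormal looks like no change. And the two-class method is something the protocol states, not something it leaves open.

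**Conclusion.** The point holds in a limited form and is minor. The laboratory method stated in Section 9.2.4 fits the synopsis measure of change in chemistry parameters poorly. It is blind to further worsening in patients abnormal at entry and to movement within the normal range. The practical gap is the part of that worsening that causes neither symptoms nor a treatment change; the rest can reach the adverse event comparison.

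The size of the gap cannot be fixed from the documents, because the share of patients abnormal at entry is not given. The range of 308 to 1232 patients rests wholly on the assumed 10% to 40%. The conclusion itself needs only that the entry criteria admit some such patients, which they do. It does not support a claim that renal safety goes unexamined, or that the trial would miss a renal signal with any stated probability.

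**What to change.** In Section 9.2.4:

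1. Keep the crosstab as description, and show all before/after cells by arm.
2. Add a descriptive between-arm comparison of change from baseline in all Safety Set patients, adjusted for the baseline value, at visits named in advance. Use the log scale for creatinine and urea.
3. Add, per arm, the number of patients reaching pre-specified relative rises from their own baseline.
4. Show items 2 and 3 separately for patients normal and abnormal at entry.

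The cut-offs are for the sponsor to set before unblinding. They serve analysis only and carry no consequence for patient management.

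The cost is a short change of wording and a few more tables from laboratory data already collected, with no new visits or tests. The one drawback is more safety comparisons to read, so they should be labelled descriptive.

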Due to the post-marketing unique advantages of Qiliqiangxin Capsules in the clinical application, it has become a hot spot for many experts and scholars in China. Previous studies have shown that the drug has cardiotonic and diuretic effect, can improve the heart function of CHF rats, and increase water discharge by reducing the expression of AQP2 in the kidney [17]. It also can reduce the expression of AngII and periostin proteins in rats with heart failure after myocardial infarction and is dose-dependent [18]. The mechanism of the effect of Qiliqiangxin Capsules on improving cardiac function is related to its inhibition of myocardial remodeling [19]. Reducing the pro-inflammatory factors of cardiomyocytes and increasing the immunomodulatory effects of anti-inflammatory factors may be one of the immunopharmacological mechanisms of Chinese medicine for improving heart function in AMI rats [20]. In the clinical study of taking Qiliqiangxin Capsules for the treatment of patients with chronic congestive heart failure, it is indicated that Qiliqiangxin Capsules can improve cardiac function grading, heart failure (Lee’s) score, systolic and diastolic function, ejection fraction (EF), TCM syndrome differentiation (中医证候), quality of life and other curative indicators and safety indicators, elevate blood nitric oxide (NO) and calcitonin gene-related peptide (CGRP) levels, and decrease endothelin (ET) levels; thereby significantly improving endothelial function in patients with heart failure.

In summary, Qiliqiangxin Capsules could resolve the current problems and eliminates the essential causes that treat cardiac insufficiency from multiple pathways, multiple links and multiple targets. It reflects the advantages of compound Chinese medicine in treating heart failure from the overall treatment, and significantly reduces NT- ProBNP levels, indicating improvement of the patient's long-term prognosis. This study is a large randomized, double-blind, multi-center clinical study carried out on the basis of achieving major study results with NT-proBNP as a surrogate endpoint, adopts the incidence of composite endpoint events consisting of cardiovascular death and re-hospitalization for heart failure as the study endpoints, in order to collect the evidence-based medical evidences for long-term prognosis in patients with chronic heart failure.

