# 9.2.1. Enrollment and completion

The following information would be initially analyzed:

- Summarize the number of enrollment and completion of each center;
- Detailed list for the number of falling off and withdrawal cases, and the total abscission rate;
- Group size in different data sets;
- Case distribution of each center
- Demographic characteristics (age, height, weight, vital signs, etc.), medical history and medication history between groups

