# 9.2.3 . Efficacy analysis:

- PP analysis and FAS analysis were performed simultaneously with efficacy evaluation;
- Main efficacy evaluation index is the time when a composite endpoint event (cardiovascular death and re-hospitalization for deterioration of heart failure) occurs. The lack of primary endpoint events is considered as censored data.

The main research hypotheses are:

H0: λT / λC ≥ 1

H1: λT / λC < 1

λT and λC are the risk of endpoint events in the study group and control group respectively. The Kaplan-Meier method was used to estimate the incidence of clinical endpoints, and a Log rank test was performed for analysis between the two groups. COX proportional hazard model was used and the center was served as a covariate to estimate the hazard ratio and the 95% confidence interval. The composite endpoints, cardiovascular death and rehospitalization for deterioration of heart failure, were analyzed separately.

- - Secondary efficacy indicators:
    - All-cause mortality
    - Composite endpoints (given up treatment due to worsening heart failure, successful cardiac arrest after resuscitation, malignant arrhythmia, non-fatal stroke)
    - Cardiovascular death and re-hospitalization for decompensated heart failure in patients with coronary heart disease
    - Serum NT-proBNP: statistical analysis of measurement data between groups.

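### Section 9.2.4 names only a before-versus-after comparison for vital signs, which does not separate a drug effect from background change in a placebo-controlled trial

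*Protocol*

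**What the plan says.** Protocol section 9.2.4 gives on-treatment vital signs a single sentence: "Indexes of vital signs are compared between before and after treatment". It names no arm.

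The neighbouring analyses are worded differently:

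- **Adverse events (9.2.4):** "Data of adverse events (case number, times and incidence of various adverse events) are compared between the two groups".
- **Laboratory values (9.2.4):** a crosstab of normal before treatment against abnormal after it, in which the number and "ratio of abnormal cases are analyzed in study group and control group".
- **NT-proBNP (9.2.3):** "Serum NT-proBNP: statistical analysis of measurement data between groups".

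Vital signs also appear in two other analysis or reporting statements. Section 9.2.1 lists them among characteristics to be described by group: "Demographic characteristics (age, height, weight, vital signs, etc.), medical history and medication history between groups". That concerns the patients as enrolled, not change on treatment. Section 7.4 says "The results from protocol mandated laboratory tests and vital signs will be summarized and give possible interpretation", which names no contrast.

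**The concern.** The trial is randomized and placebo-controlled, so the reference for a change on the drug is the change on placebo. Follow-up runs from 12 up to 36 months on background therapy that may be adjusted (section 3.3.1), and blood pressure and heart rate can move in both arms for reasons unrelated to the study drug. A before-after comparison adds that movement to any drug effect.

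Showing the before-after result for each arm side by side does not repair this. Two within-arm tests do not estimate the difference between arms: they can disagree by chance when the drug does nothing, and agree when it does something.

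Blood pressure is a relevant safety measure here. Section 1.3 says "Previous studies have shown that the drug has cardiotonic and diuretic effect", and section 4.2 names volume depletion first in its list: "AEs of interest (volume depletion, renal events, etc". For such a drug the between-arm difference in blood pressure is the quantity a reader needs.

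**Working it through.** There is no stated figure to reproduce; the point rests on wording. The first step sets out the wording, and the rest illustrate its effect.

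**1. Is the arm comparison supplied elsewhere?** Section 9.2.1 covers characteristics at enrolment. Section 7.4 promises a summary. The general rule in section 9.2 concerns the comparison of the patients' general situation; for quantitative data it names a paired t test or a Wilcoxon rank sum test, and no two-sample t test. None of these gives a between-arm comparison of vital-sign change.

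**2. Inputs for the illustration**

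| Input | Value | Source |
| --- | --- | --- |
| Patients per arm | 1540 | Protocol 2.2 |
| Test level | 0.05 two-sided | Protocol 9.2 |
| SD of change in blood pressure | 10, 12, 15 mmHg | Assumption |
| Drift shared by both arms | 0.5, 0.75, 1 mmHg | Assumption |
| Smaller number measured | 1200 per arm | Assumption |

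**3. No drug effect: how often do the two before-after tests disagree?**

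Within-arm SE = SD/√n. For n = 1540 this is 10/√1540 = 0.255, 12/√1540 = 0.306 and 15/√1540 = 0.382.

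Probability that one arm's test is significant: p = Φ(drift/SE − 1.96) + Φ(−drift/SE − 1.96). The arms are independent, so the probability that exactly one is significant is 2p(1 − p).

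| Drift (mmHg) | p at SD 10 / 12 / 15 | Exactly one arm significant |
| --- | --- | --- |
| 0.5 | 0.501 / 0.373 / 0.258 | 0.500 / 0.468 / 0.383 |
| 0.75 | 0.837 / 0.689 / 0.501 | 0.273 / 0.429 / 0.500 |
| 1 | 0.975 / 0.905 / 0.744 | 0.048 / 0.172 / 0.381 |

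The range is 0.048 to 0.500. With 1200 per arm it is 0.124 to 0.487. A between-arm test of change has a false-positive rate of 0.05 whatever the shared drift.

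Disagreement depends strongly on the drift. At a shared drift of 2 mmHg both arms are almost always significant, and disagreement falls to about 0.001 or less at 1540 per arm. The error then takes another form: with no drug effect, a change in the active arm is declared significant with probability at least 0.9995.

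**4. A real drug effect: do the two tests show it?**

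Suppose both arms fall by 2 mmHg and the drug lowers pressure by a further 2 mmHg. The active arm falls by 4 and the control arm by 2. Both before-after tests are significant with probability 1.000, 1.000 and 0.9995 for SD 10, 12 and 15, so on significance alone the arms look the same.

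Between-arm SE = SD × √(2/n) = 0.360, 0.432 and 0.541. Power to detect the 2 mmHg difference, Φ(2/SE − 1.96), is 1.000, 0.996 and 0.959. With 1200 per arm it is 0.998, 0.983 and 0.904.

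**The case against.** The strongest reply is that this is detail for a statistical analysis plan, which section 9 says will be written and which is not shown. The sentence does not forbid an arm comparison. It directly follows a laboratory analysis that is itself a descriptive before-after crosstab laid out by arm, so the natural reading may be that vital signs get the same layout. Section 7.4 also sends clinically significant abnormal results that meet listed conditions to the adverse event page, and adverse events are compared between arms.

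The illustration can be attacked too. The SD and drift are assumed, and the disagreement figures come from drifts near where disagreement peaks. The second scenario assumes a reader who sees only p-values. Section 9.2 requires means and SDs, and with SE 0.382 the 95% intervals would be about −4 ± 0.75 and −2 ± 0.75, which do not overlap. Finally, the diuretic statement in section 1.3 leads into findings in rats, not a human blood-pressure signal.

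Much of this stands. The laboratory analysis names both arms but states no test between them. Clinically important effects have another route to a between-arm comparison. By-arm means and SDs, if reported, would let a reader derive the difference. What remains is that the protocol does not leave the contrast open: it states one, and it is the weaker one. An analysis plan that followed the sentence literally would carry it forward. A by-arm display would still leave the reader to work out the difference between arms.

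**Conclusion.** The point holds, and it is minor. As written, section 9.2.4 names a within-arm contrast for vital signs, and nothing else in the protocol provides the between-arm one. Under the assumed SD of 10–15 mmHg and shared drift of 0.5–1 mmHg, two before-after tests would disagree 5–50% of the time with no drug effect (12–49% at 1200 per arm). A between-arm test keeps 5% false positives and would detect a 2 mmHg difference with 96–100% power (90–100% at 1200 per arm). These figures illustrate the problem and do not predict what the trial will show; they presume that each arm is judged by its own p-value.

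No efficacy analysis, sample-size figure or stopping rule depends on this sentence. Volume depletion and renal events are compared between arms as adverse events.

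**What to change.** Replace the vital-sign sentence in section 9.2.4 with:

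> Change from baseline in vital signs (blood pressure, heart rate) will be compared between the study and control groups, adjusted for the baseline value, and reported as a difference with 95% CI. Within-group before-after changes are descriptive only.

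The cost is one sentence. It uses data already collected and has no effect on conduct.
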